### Data monitoring

#### Data monitoring

A data monitoring committee was deemed unnecessary from the Institutional Review Board of the University of New Mexico Human Research Review Committee in that the study does not involve more than minimal risk to subjects.

#### Harms

If an adverse event is reported, the evaluation coordinator consults with the PI to address the issue, and the PI will report the event to the Institutional Review Board of the University of New Mexico Human Research Review Committee.

#### Auditing

The Clinical Supervisor audits the clinical records in the EHR on a weekly basis to ensure the PSWs are adhering to established clinical documentation practices. All paper and digital research records are reviewed for accuracy on a quarterly basis and discrepancies are noted, discussed and corrected.

### Ethics and dissemination

#### Research ethics approval

The study protocol, including recruitment, consent and data collection tools was reviewed and approved by the Institutional Review Board of the University of New Mexico Human Research Review Committee (HRRC 19–174). All participants provide informed written consent prior to enrollment in the study.

#### Protocol amendments

All protocol amendments are submitted to and approved by the University of New Mexico Human Research Review Committee.

#### Confidentiality

To assure confidentiality all study personnel are trained and certified in basic human subject’s research protections by the University of New Mexico Human Research Review Committee CITI Training Program. In addition, the PI administers ongoing training and supervision of the evaluation coordinator to assure confidentiality and privacy for participants and participant data.

#### Data sharing

The datasets generated during and/or analyzed during the current study are not expected to be made available due to not obtaining consent from participants during the consent process to share raw data beyond the purposes of the main study.

## Discussion

Our study will expand on previous research related to the implementation of treatment strategies for patients presenting at EDs and admitted to medical inpatients units wherein there is a significant window of opportunity to link patients with follow-up behavioral and clinical services for alcohol and/or drug misuse. Study findings have the potential to inform hospital-based approaches to the identification of individuals at risk of a SUD and their linkage to and retention in SUD treatment. Each intervention component in our multi-level intervention strategy has proven to be effective for our target population but information is lacking on whether all these approaches together are feasible and effective in improving patient health outcomes. Combined intervention strategies have been successful in HIV research (29, 54, 55) but have not been widely implemented or evaluated in the area of addiction (56).

Three main challenges have surfaced early on in the implementation of this study that have resulted in lower than anticipated enrollment of individuals in treatment and ultimately in the study. The first challenge relates to the high rate of PSW turnover. Over a period of six months, we have hired seven PSWs, of which four have resigned and two have been terminated from hospital employment. Reasons cited for resignation are consistent with those identified in the literature about challenges integrating PSWs in hospitals and other health care settings (e.g., outpatient, primary care) and include lack of integration, stigma, triggers impacting recovery, shifts that extend beyond regular work hours (e.g., 9–5), low salary coupled with high job demands and a challenging work environment and patient population (57, 58). A review of implementation challenges and recommendations for employing PSWs in EDs to support patients presenting after an opioid-related overdose (59), emphasized the importance of embedding PSWs in the work structure and setting. In practice, this would include having a designated workspace for PSWs in the ED and inpatient unit and delineating a detailed workflow. While identifying a free space for non-clinical use within these settings is often challenging, it is important to do so in that clinicians working in EDs and with PSWs have reported that integration of PSWs into the system of care is much easier when they are visible and available (60). With respect to stigma, some of our PSWs report being impacted by the stigma that they observed by staff in the ED towards those they were assisting. This stigma creates much distress and, in some cases, has served as a trigger and a threat to our PSW’s recovery in that it has brought back traumatic memories of how they, themselves, were treated by ED staff.

Several studies have reported low pay rates as a barrier to hiring and retaining PSWs (61–64). EDs are one of the most high-pressure environments within any hospital; the busy and constantly changing environment can be stressful for many people to work in, including PSWs. We have implemented several strategies to address these challenges. First, we identified a designated spot for our PSWs to work from and documented a detailed workflow. To increase the likelihood of integration of our PSWs within the ED and inpatient units, we have identified a designated workspace in the ED and also provide scrubs for our PSWs to wear, should they choose to do so. To address stigma, we have conducted widespread education among hospital personnel focusing on the role of PSWs, the benefits of including PSWs on a treatment team, risk factors associated with SUD and rates of recovery from a SUD when provided access to evidence-based treatment. Based on a review of peak hours in our ED, PSWs provide coverage seven days a week from 7:00 am to 6:30 pm. To increase the likelihood of success of our PSWs, we offer full-time as well as part-time positions and hire those who have a longer history of recovery. We also provide extensive initial and ongoing training; something that has been identified to be important to PSWs (65, 66). During the interview process, we focus on openness with applicants, including a transparent discussion around the challenges of working in the ED (e.g., ED pace and unpredictability, need for flexibility and task-switching) and with this patient population.

The second challenge is stigma towards individuals with SUD among providers in the ED, including emergency physicians and nursing staff. Stigma toward people who use substances (PWUS), including alcohol and illicit drugs arises from multiple sources, including policies and individuals who carry out policies (“structural stigma”) and health professionals (“provider-based stigma”). These types of stigmas can intersect with each other and compound negative effects (67). When PWUS anticipate or experience stigma, it impedes access to care, including pharmacotherapy for SUD (68), health services (69–72) and harm reduction programs (73). We have implemented two targeted strategies to address stigma among our hospital-based providers. The first strategy is developing laminated posters (48” x 60”) of success stories of several patients who have been enrolled into our study thus far and hanging them on walls in the ED and on an inpatient unit. The posters provide an overview of their history of addiction and how and why they ended up at the hospital. The poster also highlights improvements from baseline to follow-up (60 days and 120 days) in PTSD symptom severity, and drug and/or alcohol use and other key outcomes. Noteworthy is that the poster includes direct quotes from the patients that we are showcasing about the direct impact that the PSW has had on their lives and the importance of health care providers in supporting their recovery. The second strategy that we have implemented is a “Change the World” initiative that publicly recognizes ED and inpatient unit staff who (1) are committed to the highest quality care for individuals with SUD, and (2) have been noticed first-hand by our PSWs as treating individuals with SUD with kindness and respect. On a weekly basis, the team identifies hospital staff who fit either of these criteria and then one of our PSWs provides them with a personalized laminated globe that is signed by all of our clinical team and says “How Do You Change the World: One Person at a Time”. Since implementing the campaign, we have seen laminated Change the World Globes hanging on walls in physician and nursing staff cubicles and used as bookmarks.

The third challenge is the difficulty in engaging and retaining individuals in treatment. Challenges to substance use treatment engagement and retention are common (74, 75). In this particular study, while the participants have presented to the ED for injuries or illness related to the SUD (e.g., cirrhosis, pancreatitis), they may or may not make this connection and therefore may not be considering treatment for SUD. This could have a subsequent impact on their motivation for change, especially during the contacts that occur after their hospital encounter. It is also possible that within the initial meeting the PSWs do not have the opportunity to establish adequate rapport to assure that the relationship is of enough importance to ensure participant’s continued investment in further interactions. Examples of variables that may have impacted this are length of time the individual had been in the ED or inpatient unit, and the patient’s lack of alertness - due to intoxication and/or medications - during conversations with the PSW. This may account for some participants reportedly not remembering who the PSWs are when they are contacted post discharge and showing a reluctance to engage. Research on barriers to substance use treatment is extensive, with a recent overview of systematic reviews reporting 37 structural barriers (e.g., long waiting lists, expensive costs, insufficient options for treatment), 21 individual barriers (e.g., fear of stigma, motivational factors, psychiatric comorbidities), and 19 social barriers (e.g., difficulties with establishing a non-drug use network of friends, no supportive family) (76). There are barriers specific to our target population that are noteworthy. First, given that individuals are being recruited from the ED or medical inpatient, once discharged they are likely dealing with complex health and life circumstances that take priority over SUD treatment (77). Second, our intervention is based in a hospital that serves rural and tribal communities, and in both of these communities stigma, misinformation, mistrust and the lack of anonymity discourages individuals from seeking care (78, 79). Third, while providing services via telehealth could be perceived as being within the community, it may be that for certain participants, their preference may still be community-based providers and face-to-face interactions, versus this model of care. Finally, some of our patients from rural areas have had difficulty connecting to telehealth services because of not having broadband internet service; a challenge that has been reported in the literature on barriers to telemedicine in tribal communities (80). We have implemented several strategies to reduce barriers to care and hopefully decrease the low engagement and retention in treatment rates. First, when needed, we are providing individuals with cell phones and paid monthly cell phone plans so that they can access care provided via telehealth and to stay in contact with their PSW as well as research team. The phone comes preloaded with contact numbers for their PSW, the 988-crisis line, and Zoom and Teladoc apps to access telehealth appointments. The client has unlimited talk, text and data as long as they are engaging in services. If a client stops responding to calls and messages, they are given multiple reminders to re-engage and after six weeks of non-responsiveness, phone service is discontinued. Second, we are contacting patients multiple and various times throughout the day to schedule their appointments and are even willing to meet with patients after regular business hours if need be.

These challenges highlight the realities of implementing a new intervention, that includes hiring and training staff, in addition to attempting to change practices and behaviors within a complex health care system in a short period of time. We hope that the discussion of our challenges and the strategies that we have implemented thus far to address them will not only inform the field but better equip hospital leaders, administrators and clinical directors who are considering a hospital-based intervention to improve care for patients with SUD.

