### Surveys completed by hospital staff and PSWs

To further our understanding of feasibility, we are also collecting data from hospital personnel on perceived acceptability, appropriateness, and feasibility of the screening component of our intervention. Acceptability refers to how those targeted and involved in implementing the program react to the screening. Appropriateness refers to the extent to which the screening fits within the ED and medical inpatient settings. Feasibility refers to the extent to which the screening can be successfully implemented within the ED and medical inpatient settings. These constructs will be measured by three established self-report measures: the (i) Acceptability of Intervention Measure (AIM), (ii) Intervention Appropriateness Measure (IAM), and (iii) Feasibility of Intervention Measure (FIM). The AIM, IAM and FIM include 4 items rated on a 5-point Likert scale ranging from “completely disagree” to “completely agree” (53). Higher scores indicate higher perceptions of acceptability, appropriateness, and feasibility. The measures take approximately one minute each to complete. They will be completed online by PSWs on the study team and all providers within the ED and inpatient settings, including nurses, emergency physicians, inpatient physicians and other clinical support staff. Since these instruments were not designed to be completed by those who receive the intervention, we intentionally included the Client Satisfaction Questionnaire-8 [75} as part of the battery of measures (see **Table 1**) to provide an opportunity for participants enrolled in the study to voice their opinions about the acceptability of the intervention.

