### Data management

Participants are assigned a participant ID number at the first stage of data processing. The participant ID number is then added to an excel file which links the participant’s identifying information to their corresponding ID number. The excel file is kept on password protected computers and the linking information will be deleted at the end of data collection. Data are never directly linked to participant identifying data. Only research team members have access to the participant ID numbers. All data are entered into a REDCap database. The REDCap database is also password protected and only the research team has access to the data. All data will be maintained and archived or destroyed for six years after the study closes then will be destroyed.

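### Selected participants' 60- and 120-day improvements on both primary-outcome domains are displayed in the recruitment setting during enrolment, an avoidable risk of expectancy bias in a pre-post study with no comparator

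*Protocol article*

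**What the plan says.** In the Discussion, under the second challenge (provider stigma), the protocol reports posters of 48 by 60 inches presenting favourable accounts about "several patients who have been enrolled into our study thus far and hanging them on walls in the ED and on an inpatient unit". Each gives the person's addiction history and the route to hospital. On results, "The poster also highlights improvements from baseline to follow-up (60 days and 120 days) in PTSD symptom severity, and drug and/or alcohol use", along with other key outcomes. In addition, "the poster includes direct quotes from the patients that we are showcasing about the direct impact that the PSW has had on their lives". The declared purpose is provider-facing: "We have implemented two targeted strategies to address stigma among our hospital-based providers".

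Other sections give the context:

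- **Outcomes (Table 1) and Effectiveness of the multi-level intervention:** PTSD symptom severity and substance use are the two primary outcomes. The analysis is a pre-post multilevel regression, with 120 days post-baseline as the primary endpoint.
- **Eligibility criteria:** participants come from the ED and the medical inpatient units.
- **Participant interviews and consent:** the research team obtains consent and collects all interview data by phone or video.
- **Surveys completed by hospital staff and PSWs:** acceptability, appropriateness and feasibility of the screening component are rated by staff. "They will be completed online by PSWs on the study team and all providers within the ED and inpatient settings".
- **Data management:** "Data are never directly linked to participant identifying data". Access to the study database is limited to the research team.
- **Data sharing:** datasets are not expected to be released, "due to not obtaining consent from participants during the consent process to share raw data beyond the purposes of the main study".

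**The concern.** Interim results on the primary outcomes are normally kept away from people who have yet to supply outcome data. Here a favourable selection of them hangs where such people are recruited. The posters tell a prospective participant, and the peer worker who may go on to treat that person, which measures the team counts as success and which way they are expected to move. Both primary outcomes are interview-reported, and in a pre-post analysis without a comparison group any resulting change in reporting is counted as treatment effect.

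There are two lesser points. The staff who rate the screening component work among the posters, so ratings given after posting are not independent of them. And displaying an individual's study results next to that person's history and words is hard to square, on its face, with the protocol's statements on how participant data are held and used.

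**Working it through.** **Is the display inside the study's active period and setting?**

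1. *Content.* PTSD severity and drug or alcohol use at 60 and 120 days (Discussion) match the two primary outcomes and the primary endpoint time (Table 1; Effectiveness section).
2. *Selection.* Only successes are shown, so the displayed results are favourable by construction.
3. *Place.* The ED and one inpatient unit (Discussion); recruitment is from the ED and the medical inpatient units (Eligibility criteria).
4. *Time.* The Abstract states an aim of 110 participants, and the Discussion describes enrolment as running behind expectation. Recruitment is therefore continuing while the posters hang.
5. *Protection in the design.* The study is non-randomised (Study design), the primary analysis is pre-post, and no comparison group is described. The article names no safeguard against poster exposure.

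**How much could it matter?** No figure in the protocol sizes the effect. The following is an illustration on assumed inputs. It uses the paired t-test and N = 101 from the Sample size section, and assumes a two-sided 5% level and no true change. A fraction f of participants is influenced by the posters, and their pre-post change shifts by b standard deviations (SD). Both f and b are assumptions.

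- Mean shift = f × b
- SD of change = √(1 + f(1 − f)b²)
- Noncentrality = √N × f × b / SD

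For f = 0.5 and b = 0.2, the mean shift is 0.10 and the SD is √(1 + 0.25 × 0.04) = 1.005. The noncentrality is 10.05 × 0.10 / 1.005 = 1.00, and the rejection rate is 16.8%.

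| f | b (SD) | Mean shift (SD) | Rejection rate, no true change |
|---|---|---|---|
| 0.25 | 0.1 | 0.025 | 5.7% |
| 0.50 | 0.1 | 0.05 | 7.9% |
| 0.50 | 0.2 | 0.10 | 16.8% |
| 0.50 | 0.3 | 0.15 | 31.5% |
| 0.75 | 0.3 | 0.225 | 60.3% |

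The table shows only that a small shift in part of the sample is not harmless when there is no comparator. It does not show that such a shift occurs. If exposure moves baseline and follow-up answers equally, b is zero and the change score is unaffected. If it moves baseline more, the sign of the bias depends on which way baseline moves.

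**Data-protection sections side by side.** Data management bars direct linkage of data to identifying data and restricts database access to the research team. It also describes a separate file linking ID numbers to identities, so tracing a result to a person is possible within the rule. Data sharing concerns raw datasets. The Discussion describes individual improvements shown with history and quotations, but does not say whether names or photographs appear or whether the showcased participants gave separate permission.

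**The case against.** The strongest reply is that exposure is partial and the route to bias is weak. The posters are aimed at providers. They hang on one inpatient unit, whereas Study site lists three (two medical-surgical, one intensive care). A new participant would generally see one before baseline, with treatment and interviews following remotely after discharge. Peer workers do not conduct the interviews. The Discussion reports that some patients were not alert in hospital and later did not remember the peer worker, so a lasting poster effect at 120 days is uncertain. Some expectancy is present in any open study without a control arm. All of this stands. It rules out saying that outcomes are biased, or that every later participant is exposed. It does not remove the risk or supply a reason to keep study results on the wall.

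On staff ratings, the scales concern screening and not treatment outcomes, their timing relative to the posters is not given, and changing staff attitudes is an openly described implementation strategy. That also stands. The remaining point is one of interpretation: ratings taken after posting describe screening with the posters in place.

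On data protection, a reader might infer that the posters break the protocol's own rule. The documents do not support that. The linkage statement concerns how data are stored, the consent statement concerns raw data, and a summary of one person's improvement is not a raw dataset. Direct quotations suggest that those shown cooperated, and a condensed article may omit the permission arrangements.

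A reader might also infer that the posters deter enrolment, because the Discussion says lack of anonymity discourages care-seeking in these communities. That remark is general and does not mention the posters.

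**Conclusion.** The point holds as a risk to validity that the study can avoid at little cost. Favourably selected results on both primary-outcome domains, up to the primary endpoint time, are on view in the recruitment setting during enrolment, and the pre-post design cannot absorb any expectancy or social-desirability effect that follows. The size and direction of any bias are unknown. The illustrative rejection rates, 5.7% to 60.3% against a nominal 5%, rest entirely on the assumed f and b.

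Staff ratings are affected only in that those collected after posting include the posters' influence. The data-handling question is a tension to be reconciled and not an established contradiction. The conclusion assumes that recruitment and 120-day follow-up were still under way while the posters were up, as the Discussion indicates.

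**What to change.** 1. Remove study outcome scores and baseline-to-follow-up changes from the posters until the last 120-day interview is complete. Keep the anti-stigma stories without study results.
2. Record the date the posters went up. As a descriptive sensitivity check only, report primary outcomes and staff scores before and after that date, where data exist on both sides.
3. Do not add a before/after-poster term to the primary models. It would be confounded with peer-worker turnover, staff education, the staff-recognition campaign, phone provision and the other programme changes described in the Discussion, and those models already carry many covariates for roughly 100 participants.
4. Reconcile the Discussion with Data management and Data sharing: state whether the posters are identifiable and whether those shown gave separate permission for this use.

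The cost is reprinting a few posters, a date in the study log, a short descriptive table and a few sentences of text. The downside is a slightly less persuasive anti-stigma message until follow-up ends.

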### Participant interviews and consent

Once an individual agrees to engage in treatment, the PSW provides details about the opportunity to participate in a prospective follow-up cohort study. Individuals who are interested in participating sign a release of information agreeing to be contacted by a member of the research team. A member of the research team is then responsible for contacting individuals to provide further information about the study, obtaining consent for those who agree to participate and conducting baseline and follow-up interviews. Follow-up interviews are being conducted every 60-days post baseline. The consent process and all data collection is conducted by phone or a HIPAA compliant video conferencing platform. Individuals are compensated for their participation in the study with a $60 merchandise gift card for completing the baseline interview and $90 for every follow up assessment. The research team makes multiple attempts at varied times of the day and day of the week to consent individuals and complete baseline and follow up interviews. Participants are contacted via phone, text, mail and email. Participants are also offered a phone with monthly cell phone service to increase the likelihood of their participation in the study. Interviews range between 45 and 60 minutes. **Table 1** provides an overview of all data being collected during participant interviews, including the data collection tools and time point.

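### Study phone service is tied to treatment engagement and ends after six weeks of silence, with no stated exception for cohort members whose phone or video outcome interviews are still due

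*Protocol article*

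**What the plan says.** Two sections of the protocol article describe the phones.

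- **Participant interviews and consent.** On mode: "The consent process and all data collection is conducted by phone or a HIPAA compliant video conferencing platform". Interviews fall every 60 days after baseline. On the phone: "Participants are also offered a phone with monthly cell phone service to increase the likelihood of their participation in the study". On contact routes: "Participants are contacted via phone, text, mail and email".
- **Discussion, third challenge (engagement and retention).** Phones go to a subset: "when needed, we are providing individuals with cell phones and paid monthly cell phone plans". They serve telehealth access and also allow people to "stay in contact with their PSW as well as research team". The condition on service is: "The client has unlimited talk, text and data as long as they are engaging in services". For clients who stop responding to calls and messages, the rule is that "they are given multiple reminders to re-engage and after six weeks of non-responsiveness, phone service is discontinued".

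Table 1 and the effectiveness section make the PCL-C and the Addiction Severity Index the two primary outcomes, both measured at baseline and every 60 days. The last paragraph of the statistical methods puts the primary endpoint at 120 days after baseline. Only the utilisation outcomes draw partly on the health record.

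**The concern.** A phone that is also meant to support outcome follow-up is withdrawn according to treatment engagement. Leaving treatment is not the same as leaving the cohort. A participant may stop answering a peer worker's scheduling calls and still be willing to give a compensated research interview. If that person's only usable line has been switched off, neither primary outcome can be collected.

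The design makes this matter. Effectiveness is judged from within-person change with no comparison group, so if people who disengage are under-represented at day 120, the shortfall passes directly into the estimated change. The probable direction is towards improvement, because those who left treatment are likely to have changed less. The Discussion itself reports low engagement and retention, and some patients who did not remember the peer worker after discharge, so early silence is foreseeable.

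**Working it through.** The plan gives no figure for follow-up loss, so there is none to reproduce. The check has three parts.

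**1. Timing.** Inputs: six weeks of non-responsiveness (Discussion), interviews every 60 days (participant interviews), primary endpoint at day 120 (statistical methods).

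- Six weeks = 6 × 7 = 42 days.
- Service ends before the day-60 interview if the last response was before about day 60 − 42 = 18.
- Service ends before the day-120 interview if the last response was before about day 120 − 42 = 78.

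The day-60 interview is threatened only if silence starts within about 18 days of baseline. The day-120 endpoint is exposed to silence starting over a much longer period.

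**2. Effect on mean change.** The documents do not give the share holding a study phone, the share who disengage, or the difference in outcome between the two groups. Assume for illustration that 30% disengage and do not change, and 70% stay engaged and change by d. The true mean change is 0.70d. Let f be the fraction of the disengaged who are lost because their service ended, with everyone else interviewed. Then

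observed mean = 0.70d / (1 − 0.30f), and overstatement = 1 / (1 − 0.30f) − 1.

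| f | Observed mean | Overstatement |
|---|---|---|
| 10% | 0.70d / 0.97 = 0.72d | about 3% |
| 25% | 0.70d / 0.925 = 0.76d | about 8% |
| 50% | 0.70d / 0.85 = 0.82d | about 18% |

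Only losses caused by the disconnection belong in f. If half of the disengaged are missed in total, but 25% of the disengaged would have been unreachable with a working line, the part due to the rule is 0.925 / 0.85 − 1 = about 9%, not 18%.

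**3. The same question in SD units.** Let q be the share who disengage, and suppose their mean change is worse than that of the engaged by δ SD. Then bias = δ × (q − q among those interviewed). Take q from 30% to 50%, δ from 0.3 to 0.5, a true mean change of zero and 110 enrolled, tested by a two-sided paired t-test at 0.05.

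- 10% of the disengaged rely on a study phone, and half to all of those are lost: overall loss 1.5% to 5%, bias 0.003 to 0.013 SD, false-positive rate about 5%.
- 60% rely on it and all are lost: overall loss 18% to 30%, bias 0.05 to 0.11 SD, false-positive rate about 7% to 15%.

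The result runs from negligible to material, and the documents do not give the inputs to narrow it. The margin for loss is small in any case: 110 enrolled against 101 required leaves 9 people, or 9 / 110 = 8.2%.

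**The case against.** A reader might infer that patients who disengage will in general be lost to follow-up. The documents do not support that. Phones are given by need, so the rule reaches only people who hold a study phone and have no other phone or video access. Anyone else can still be interviewed. Mail, email and repeated attempts remain as ways of making contact, although the interview itself still needs a phone or video link. No follow-up loss by engagement or phone status is reported.

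A reader might also take the trigger to be silence towards the treatment team alone. The wording about engaging in services and re-engaging points that way, but the text speaks only of calls and messages, and the phone also serves contact with the research team. Whether answering a research call keeps service on is not stated. Nor is it stated that the phone offered for study participation falls under the same cut-off, and a fuller protocol may settle this.

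Third, someone silent for 42 days despite repeated reminders on a working line may not be interviewed even if service continues. It would therefore be wrong to charge this rule with the loss of, say, half to three quarters of everyone who disengages.

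Finally, the planned models include motivation to change and treatment satisfaction, which are related to engagement, and the activity logs record sessions completed, so loss can be examined by engagement. That softens the concern without removing it: attendance is not among the listed model terms, and examining loss afterwards does not recover a missing interview.

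These points limit the reach and size of the problem. They leave in place a stated cut-off with no exception for interviews still due.

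**Conclusion.** The concern holds as an avoidable risk of outcome-related missing data among participants who depend on a study phone. It does not hold as a demonstrated selective loss of everyone who disengages. Service conditional on engagement can end before the day-120 primary endpoint for a phone-dependent participant whose last response was before about day 78, and before the day-60 interview if it was before about day 18. The probable direction of bias is towards improvement.

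The size cannot be fixed from the documents. An overstatement of about 3% to 18% rests on the assumptions that 30% disengage without change and that 10% to 50% of them are lost through the cut-off. It shrinks to the extent that those people would have been missed anyway. This is a cheap improvement worth making, not a flaw that invalidates the design.

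**What to change.** Reconcile the section on participant interviews and consent with the Discussion. State that every consented cohort participant given a phone keeps service through the day-120 interview window, whatever their engagement in treatment, unless they withdraw from the study. Apply the six-week cut-off only after that window, or to people who are not in the cohort.

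The cost is a short amendment and a few extra months of basic phone service for the subset who hold a study phone and stop responding. It needs no added staff or procedures.
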